**2.2 Secondary Objectives**

- Pharmacokinetics (PK) indicator (Cmax)

The peak concentration of allo-DNT cells amplified in the peripheral blood (Cmax, detected by Flow Cytometry). Time Frame: Up to 2 years.

- Pharmacokinetics (PK) indicator (AUC)

Allo-DNT cells blood concentrations will be measured at different time points to evaluate the area under the curve (AUC). (AUC, detected by Flow Cytometry). Time Frame: Up to 2 years.

- Pharmacokinetics (PK) indicator (Tmax)

Allo-DNT cells blood concentrations will be measured at different time points to evaluate the peak time (Tmax) in peripheral blood. Tmax is defined as the time to reach the highest concentration (Tmax, detected by Flow Cytometry). Time Frame: Up to 2 years.

- Pharmacokinetics (PK) indicator (T1/2)

Allo-DNT cells blood concentrations will be measured at different time points to evaluate the elimination half-life in hours (T1/2). T1/2 is defined as the time point when the concentration of allo-DNT reaches half of maximum in a patient’s peripheral blood (T1/2, detected by Flow Cytometry). Time Frame: Up to 2 years.

- Recurrence rate at 6 months

Record the proportion of patients with recurrence in the study. Time Frame: Up to 6 months.

- Relapse-free survival (RFS)

Relapse-free survival is the time from study enrollment until documented disease relapse, or death from any cause. Time Frame: Up to 2 years.

- GvHD-free and relapse-free survival (GRFS)

GRFS is the time from study enrollment until documented disease relapse, or death, or GvHD occur from any cause. Time Frame: Up to 2 years.

- 2-year overall survival

From the date of entry into the clinical study until death from any cause. Time Frame: Up to 2 years.

1. **TRIAL DESIGN**

The trial is divided into two parts: Part A is a dose escalation trial with two dose groups (1.0×10^8 cells/kg, 1.5×10^8 cells/kg at day 0, day 28 and day 56), with 6-12 patients planned to be enrolled. Part B is a dose-expansion randomized controlled trial in which 40-60 patients will receive RC1012 infusions at recommended phase II dose (RP2D) levels. Patients at the end of the infusion will continue to be followed up for a total of 2 year.

1. **ELIGIBILITY**
   1. **Subject Eligibility**
      1. **Inclusion Criteria**

- Voluntarily sign an ICF and expect to complete the study procedures for follow-up examinations and treatment.
- Aged 18 to 70 years (including cut-offs), regardless of gender.

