- Subject has been involved in other clinical studies within 3 months prior to screening.
- Subject in the judgement of the investigator and/or clinical criteria, is contraindicated to any study procedure or have other medical conditions that may place them at unacceptable risk.
  - 1. **Criteria for Removal from the Study**
- The occurrence of intolerable toxicity during infusion prevents the subject from continuing RC1012 injection treatment.
- The subject may choose to withdraw from the clinical trial at any time by informing the researcher.
- Hematologic relapse of the patient’s disease occurs, and the researcher evaluates that cell infusion is not appropriate.
- The subject experiences death, withdrawal of informed consent, or is lost to follow-up during the trial.
- Other situations where the researcher deems cell infusion inappropriate.
  1. **Donor** **Eligibility**
     1. **Inclusion Criteria**
- Age ≥ 18 years old.
- Healthy person who meets the requirements of blood donation in central blood station.
- There is no disease that can be transmitted through blood within 30 days before blood collection (HIV, HBsAg, HBcAb, HCV antibody, syphilis serological test, CMV IgM, and EBV IgM all negative).
- The cytotoxicity of DNTs to at least three myeloid leukemia cell lines (OCI-AML3, MV 4-11, K562, U937, etc.) (target to efficiency ratio 4:1) ≥ 20%, or to patient primary AML cells ≥ 10%.
  - 1. **Exclusion Criteria**
- There are chronic diseases that need to be treated, such as hypertension, diabetes, heart disease, thyroid disease and liver and kidney insufficiency.
- Bone marrow diseases.
- Pregnancy.
- Systemic glucocorticoids must be used before peripheral blood taking.
- Paroxysmal psychosis.
- Poison and drug addiction.

1. **TREATMENT PLAN**
   1. **Ex vivo expansion of DNTs and Infusion**

According to the established expansion method (Patent number: PCT/CA2006/001870), DNTs will be expanded *ex vivo* under GMP conditions. DNTs will be assessed for purity and microorganism and endotoxin contamination before infusion. After enrollment, patients will receive once a month with total three times infusion of DNTs product at escalating doses of 1×10^8^, or 1.5×10^8^/kg. Subjects' vital signs will be assessed, and pulse oximetry will be done during the infusion.

- 1. **Supportive Treatment**

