- Serum Cytokine Levels: Cytokines will be measured before infusion of DNTs, then 6, 24, 48 hours, 5d, 7d after each DNT infusion, and 14d, 21d, 28d after the 3^rd^ infusion. Serum cytokines included interleukin-6 (IL-6), interferon (IFN)-γ, IL-8, IL-10, tumor necrosis factor (TNF)-α, macrophage inflammatory protein (MIP)-1α, MIP-1β, monocyte chemoattractant protein (MCP-1), and soluble receptors IL-1Rα and IL-2Rα.
- Assessment of DNTs in vivo: Peripheral blood aspirates will be analyzed by FACS to assess and quantify the percentages of DNTs before infusion, then 6, 24, 48 hours, 5d, 7d after each DNT infusion, and 14d, 21d, 28d after the 3^rd^ infusion.
- Electrocardiogram (ECG): ECGs should be performed when clinically indicated.
- Bone Marrow Analysis: Bone marrow aspirates will be obtained before the first cycle of DNTs therapy and 28 days after the 3^rd^ infusion. After achieving CR, analyze once a month.
  1. **Follow-up**

Patients will be followed-up for survival data for 2 year from the date of start of treatment. Blood routine, biochemistry and bone marrow studies will be obtained monthly as clinically indicated to assess disease. Analyses will include morphologic examination of the aspirate, FACS, and cytogenetics when indicated.

1. **TREATMENT RESPONSE/OUTCOME ASSESSMENT**
   1. **Main Outcome Measurement**

Cumulative relapse rate at 6 months post-treatment.

- 1. **Secondary Outcome Measurement**

Relapse-free survival (RFS), GvHD-free relapse-free survival (GRFS), and 2-year overall survival (OS) post-cell infusion.

- 1. **Safety Measurement**
- Safety assessment indicators include vital signs, clinical laboratory tests (complete blood count, blood biochemistry, coagulation function, urinalysis), 12-lead electrocardiogram (ECG), and physical examination. Throughout the study, research center staff will monitor adverse events.
- Adverse Events (AEs): The occurrence of all AEs and serious adverse events (SAEs) will be tracked. Changes from baseline in laboratory tests (including complete blood count, urinalysis, blood biochemistry, coagulation function), 12-lead ECG, physical examination, and vital signs (temperature, respiration, blood pressure, and pulse) will be analyzed.

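### Section 4.1.3 lists reasons to stop infusion as reasons to leave the study, which conflicts with the 2-year follow-up and could bias overall survival upward

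*Protocol*

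**What the plan says.** Protocol section 4.1.3, headed "Criteria for Removal from the Study", has five items. Three concern the infusion only:

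- toxicity: "The occurrence of intolerable toxicity during infusion prevents the subject from continuing RC1012 injection treatment";
- hematologic relapse, under the further condition "and the researcher evaluates that cell infusion is not appropriate";
- an open item: "Other situations where the researcher deems cell infusion inappropriate".

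The other two concern leaving the study: the subject's own choice to withdraw, and "The subject experiences death, withdrawal of informed consent, or is lost to follow-up during the trial". The section does not distinguish stopping treatment from ending participation.

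Section 5.4 says: "Patients will be followed-up for survival data for 2 year from the date of start of treatment". It names no exception. Section 3 says: "Patients at the end of the infusion will continue to be followed up for a total of 2 year". In section 2.2, OS runs from study entry to death from any cause. For RFS the same section says: "Relapse-free survival is the time from study enrollment until documented disease relapse, or death from any cause". GvHD-free relapse-free survival (GRFS) adds GvHD as an event.

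**The concern.** A site that follows the heading would close a patient's participation when infusions stop for toxicity, relapse or investigator judgment. A site that follows 5.4 would keep the same patient under observation for 2 years. Both instructions cannot hold, and an analysis plan cannot recover data that were never collected.

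These patients are selected on prognosis. The background gives a 2-year survival below 15% after relapse, and patients who stop for toxicity may also do worse than the rest. Censoring them when they leave would be informative, and OS would look better than it is.

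Part B is described as randomized and controlled. The toxicity item names RC1012, and the other two turn on whether cell infusion is suitable. If the controls receive no infusion (the protocol does not describe the control arm), these reasons arise only among RC1012 recipients. Follow-up could then be cut in one arm, and the bias in that arm would pass in full into the difference between arms.

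**Working it through.** The protocol gives no power, effect size or dropout figure for this point, so there is no stated figure to reproduce. The check asks how far the 24-month Kaplan-Meier estimates move if removed patients are censored instead of followed.

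**Inputs from the protocol**
- Relapse 30% and 2-year OS after relapse 15% (Background, given as more than and less than these values).
- Infusions on days 0, 28 and 56 (section 3).

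**Assumptions**
- The 30% accrues over 2 years.
- Death without relapse is 10% at 2 years.
- 10% of patients stop for toxicity at some time in days 0 to 56, with hazards of relapse and of death without relapse doubled (base case). The harsh case is 20% with tripled hazards.
- All times are exponential.

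**Monthly hazards**
- relapse: r = −ln(0.70)/24 = 0.01486
- death without relapse: d = −ln(0.90)/24 = 0.00439
- death after relapse: p = −ln(0.15)/24 = 0.07905

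**True values, all patients followed**
- Without a toxicity stop: RFS = 0.70 × 0.90 = 0.630. OS = 0.630 + r(0.630 − 0.150)/(p − r − d) = 0.630 + 0.01486 × 0.480/0.0598 = 0.749.
- With a toxicity stop, hazards ×2: RFS = 0.630² = 0.397. OS = 0.397 + 0.02972 × (0.397 − 0.150)/0.0405 = 0.578.
- Base case: RFS = 0.9 × 0.630 + 0.1 × 0.397 = 0.607. OS = 0.9 × 0.749 + 0.1 × 0.578 = 0.732.

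**Censored at removal.** If every relapse leads to removal, almost the only deaths left to count are those without relapse, and the OS curve tends to exp(−24d) = 0.90. A simulation of 400,000 patients gives the intermediate cases (percent; toxicity stops are also censored):

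| Case | OS followed | OS censored | Difference |
|---|---|---|---|
| Base, relapses to day 56 only | 73.2 | 76.5 | +3.3 |
| Base, half of all relapses | 73.3 | 81.6 | +8.3 |
| Base, every relapse | 73.2 | 89.9 | +16.7 |
| Harsh, relapses to day 56 only | 69.1 | 76.4 | +7.3 |
| Harsh, every relapse | 69.1 | 89.9 | +20.8 |
| Base with 40% relapse, every relapse | 67.8 | 90.1 | +22.3 |

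The window matters because few relapses fall inside it. Day 56 is 56/30.44 = 1.84 months. Among patients without a toxicity stop, r/(r + d) × (1 − exp(−1.84(r + d))) = 0.772 × 0.0348 = 2.7% relapse by then, against 0.772 × 0.37 = 28.6% by 24 months.

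**RFS**

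| Case | Followed | Relapse removal only | Toxicity stops censored |
|---|---|---|---|
| Base | 60.6 | 60.6 | 62.8 |
| Harsh | 55.5 | 55.5 | 62.6 |
| Toxicity stops with no excess risk | 63.1 | 63.1 | 63.1 |

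Removal at relapse leaves RFS unchanged because the relapse has already been counted. The whole shift, 0 to 62.6 − 55.5 = 7.1 points, comes from toxicity stops. GRFS was not computed, since the protocol gives no GvHD rate. The logic is the same: relapse is already an event.

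**The case against.** The strongest reply is that 4.1.3 merely has a badly chosen heading. No section says that data collection ends at removal or that removed patients are censored. Section 5.4 covers patients without exception. Section 5.2 asks for medication records through the RFS and OS follow-up periods, and it bars other anti-tumor therapy only until hematologic relapse or a change of regimen, which suggests that patients are still observed afterwards. Section 7.4 follows adverse events until they resolve or stabilize. All of this stands, so the protocol cannot be said to cut follow-up. It gives two instructions and does not say which one governs.

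A reader might also infer that removal at relapse inflates RFS and GRFS. The documents do not support that, because relapse is an event in both.

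A reader might take an OS bias of some 17 to 20 points as the expected size. That needs every relapse over 2 years to lead to removal. The relapse item depends on a decision about infusion, which plausibly arises only while infusions are being given, and there the base-case effect is 3 to 4 points.

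Listing death among the removal reasons is untidy but harmless, since sections 2.2 and 6.6 define it as an event. OS, RFS and GRFS are secondary endpoints, which limits the weight of the point. The 6-month relapse rate, named as the main outcome in 6.1, is nevertheless exposed through toxicity and judgment stops.

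**Conclusion.** The point holds as a contradiction in wording with a possible bias, not as a demonstrated loss of follow-up. Section 4.1.3 treats three reasons to stop infusion as reasons to leave the study, and this cannot be squared with 5.4, with section 3 or with the OS definition.

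If removed patients were censored, 2-year OS would be too high by about 3 to 4 points in the base case when only relapses in the infusion window lead to removal, and by about 17 when every relapse does. Harsher assumptions raise both figures, as tabulated. RFS would rise by 0 to about 7 points, through toxicity or judgment stops only, and not at all if those patients carry no excess risk. GRFS and the 6-month relapse rate are exposed by the same route, but their size was not estimated.

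These sizes rest on the assumed 10% death without relapse, the assumed frequency and excess risk of toxicity stops, and exponential times. That the loss could fall on one arm of Part B rests on controls receiving no infusion.

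**What to change.** Reconcile 4.1.3 with 5.4. Keep the existing criteria and their conditions unchanged, including the investigator's judgment attached to relapse, and place them under two headings:

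- discontinuation of RC1012 infusion: the toxicity, relapse and judgment items;
- withdrawal from study: consent withdrawn or lost to follow-up.

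Add one sentence: patients who stop infusion remain in adverse event, relapse, GvHD and survival follow-up to 2 years unless they withdraw consent to that follow-up. Word section 3 so that its 2-year follow-up plainly includes patients who stop infusions early. Moving death out of the list is optional tidying.

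This takes no view on when infusions should be stopped. The cost is a wording amendment plus follow-up contacts that 5.4 already foresees.

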- Dose-limiting toxicities (DLTs) and maximum tolerated dose (MTD) (Phase I only): Cytokine release syndrome (CRS) will be graded according to the ASTCT 2019 criteria, while other AEs will be graded based on the NCI-CTCAE version 5.0. The frequency and severity of DLTs will be assessed to determine the MTD for the subjects.
  1. **Response Assessment**
- Complete Remission (CR): Bone marrow blasts < 5%; absence of circulating blasts and blasts with Auer rods; absence of extramedullary disease; ANC≥1.0×10^9^/L; platelet count ≥100×10^9^/L;
- CR without MRD (CR MRD^-^): If studied pretreatment, CR with negativity for a genetic marker by RT-qPCR, or CR with negativity by MFC;
- CR with incomplete recovery (CRi): All CR criteria except for residual neutropenia (< 1.0 ×10^9^/L or thrombocytopenia (< 100 ×10^9^/L);
- Morphologic leukemia-free state (MLFS): Bone marrow blasts < 5%; absence of blasts with Auer rods; absence of extramedullary disease; no hematologic recovery required;
- Partial Remission (PR): All hematologic criteria of CR; decrease of bone marrow blast percentage to 5% to 25%; and decrease of pretreatment bone marrow blast percentage by at least 50%;
- Treatment failure: Failure to achieve CR or PR
  1. **Relapse**
- Hematologic relapse: after achieving CR MRD^-^, CR, or CRi in AML patients, the reappearance of leukemic cells in peripheral blood or ≥5% blasts in bone marrow (excluding other causes such as bone marrow regeneration after consolidation chemotherapy), or leukemic cell infiltration at extramedullary sites.
- Molecular relapse: after achieving CR MRD^-^, the reappearance of MRD positivity detected by standard methods [e.g., RT-qPCR or multiparametric flow cytometry (MFC) with a sensitivity of at least 10^-3^].
  1. **Survival**
- Overall Survival (OS): From the date of entry into the clinical study until death from any cause.
- Relapse-Free Survival (RFS):  the time from study enrollment until documented disease relapse, or death from any cause.

1. **ADVERSE EVENT REPORTING**
   1. **Definitions**
      1. **Adverse Event**

An AE is any undesirable sign, symptom or medical condition or experience that develops or worsens in severity after starting the first study treatment in the protocol, even if the event is not considered to be related to the study.

- - 1. **Serious Adverse Event**

A SAE is any adverse event, occurring at any dose and regardless of causality that:

- Fatal
- Life-threatening
- Requires or prolongs hospital stay

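### OS, RFS and GRFS start at enrollment in Sections 2.2 and 6.6 but after cell infusion in Section 6.2, and neither 2-year follow-up statement is tied to enrollment or randomization

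*Protocol*

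**What the plan says.** **Endpoint origins.** Section 2.2 defines the three endpoints from study entry or enrollment:

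- OS: "From the date of entry into the clinical study until death from any cause".
- RFS: "Relapse-free survival is the time from study enrollment until documented disease relapse, or death from any cause".
- GRFS: "GRFS is the time from study enrollment until documented disease relapse, or death, or GvHD occur from any cause".

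Each has a time frame of up to 2 years. Section 6.6 repeats the origin for OS ("Overall Survival (OS): From the date of entry into the clinical study until death from any cause") and for RFS ("the time from study enrollment until documented disease relapse, or death from any cause"). It does not define GRFS again.

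Section 6.2, which names the secondary outcomes, gives a different origin: "Relapse-free survival (RFS), GvHD-free relapse-free survival (GRFS), and 2-year overall survival (OS) post-cell infusion". Section 3 schedules infusions on days 0, 28 and 56, and Section 6.2 does not say which of them starts the clock.

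**Follow-up.** Section 5.4 states: "Patients will be followed-up for survival data for 2 year from the date of start of treatment". Section 3 states: "Patients at the end of the infusion will continue to be followed up for a total of 2 year".

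**Sequence and groups.** Section 5.1 places infusion after enrollment and sets no maximum interval. Sections 3 and 10 call Part B a randomized controlled trial but do not describe the control.

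**The concern.** The same endpoints carry two different time origins, and patients can have events between them. A patient who relapses or dies after enrollment but before the first infusion has an RFS and GRFS event under Sections 2.2 and 6.6. Under Section 6.2 that patient has no time zero, so the event is lost. Removing early failures in this way makes the estimates look better.

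The stakes are higher in Part B. If controls are not infused, an infusion origin cannot be applied to them at all. If the cell arm were then timed from infusion and the control arm from randomization, early events would count in one arm only and the comparison would tilt toward the cells.

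Follow-up has a related problem. Both statements depend on treatment having been given, while the formal endpoint definitions do not. Data that sites never collect cannot be recovered at analysis.

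**Working it through.** The plan states no figure on this point, so there is none to reproduce. The check is day arithmetic.

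**Inputs**
- First infusion = day 0 and last infusion = day 56 (Section 3).
- Two years = 730 days.
- Enrollment = day −g. The protocol gives no value for g. I assume 0 to 30 days, for illustration only.

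**Possible ends of follow-up**
- A: Section 5.4, start of treatment plus 2 years = day 730.
- B: Section 3 read as last infusion plus 2 years = 56 + 730 = day 786.
- C: Section 3 read as 2 years in total from enrollment = day 730 − g.

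Section 3 read as 2 years in total from the first infusion is the same as A. The gap between A and B is 786 − 730 = 56 days.

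**Formulas**
- Days observed = end day − origin day.
- Shortfall = max(0, 730 − days observed).

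| Origin | End A (730) | End B (786) | End C (730 − g) |
|---|---|---|---|
| Enrollment (−g) | 730 + g = 730 to 760; shortfall 0 | 786 + g = 786 to 816; shortfall 0 | 730; shortfall 0 |
| First infusion (0) | 730; shortfall 0 | 786; shortfall 0 | 730 − g = 700 to 730; shortfall 0 to 30 |
| Last infusion (56) | 730 − 56 = 674; shortfall 56 | 786 − 56 = 730; shortfall 0 | 674 − g = 644 to 674; shortfall 56 to 86 |

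**Patients never infused.** There is no day 0, so none of the infusion origins exists, and ends A and B cannot be computed. Under Sections 2.2 and 6.6 the endpoint clock does start at entry, and Section 2.2 gives a time frame. What is missing is a rule in Section 3 or 5.4 telling sites how long to follow these patients.

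**Can such patients occur?** Yes. Two of the removal criteria in Section 4.1.3 (relapse where the researcher judges infusion unsuitable, and other situations judged unsuitable) are not limited to patients already infused. Part B controls may be a further group.

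**After the fix.** With enrollment as origin and follow-up of 2 years from it, every enrolled patient has 730 planned days and no shortfall.

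**The case against.** - **Section 6.2 is a one-line list, not a definition.** The two sections that do define endpoints agree with each other, and the infusion qualifier in Section 6.2 may grammatically attach only to 2-year OS. This is fair. It would narrow the conflict to OS but not remove it, and an analyst working from the outcomes section would still use a different time zero.
- **Section 3 may not conflict with Section 5.4.** Its wording about continuing for a total of 2 years fits a period that includes the infusions. This stands, so the 56 days are an ambiguity rather than a proven contradiction. Neither statement is anchored to enrollment on its face.
- **The interval before infusion may be short.** The Background calls the product off-the-shelf, so a long wait does not follow from ex vivo expansion. This also stands. The protocol gives neither the interval nor an event rate for it, so the number of events lost cannot be estimated from the document.
- **A SAP could settle it.** A SAP can specify censoring, but the protocol has already fixed the origin in two ways. How long sites follow patients, and which patients, is trial conduct that the protocol sets.

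A reader might infer that 2-year OS cannot be observed. The documents do not support that. Infusion follows enrollment, so follow-up under Section 5.4 gives every infused patient at least 730 days from entry.

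**Conclusion.** The contradiction over the origin is real, and it affects all three survival-type secondary endpoints, or at least OS on the narrowest reading of Section 6.2. The follow-up rules do not match the formal definitions on either origin. The infusion origin loses events before the first infusion and leaves uninfused patients without a time zero. The enrollment origin keeps them but gives no operational end of follow-up.

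The size is limited:

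- For infused patients timed from enrollment, the shortfall is 0 on every reading.
- With follow-up as in Section 5.4, the shortfall is 56 days (674 of 730) only if the origin is the last infusion.
- Reading Section 3 as 2 years in total from enrollment adds shortfalls of 0 to 30 days from first infusion and 56 to 86 days from last infusion. Those ranges depend on the assumed gap of 0 to 30 days.

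A reader might also conclude that never-infused patients have no clock at all. That goes too far, because Sections 2.2 and 6.6 give them a time zero. The concern about Part B controls is conditional on their not being infused, which the protocol does not say. Because these are secondary endpoints and the definitions in Sections 2.2 and 6.6 agree, this should be corrected but does not undermine the trial.

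**What to change.** 1. Use one time origin for OS, RFS and GRFS: the enrollment date in Part A, and the randomization date in Part B, applied identically to both arms.
2. Delete the infusion qualifier from Section 6.2, so that it refers to the definitions in Sections 2.2 and 6.6. Add GRFS to Section 6.6.
3. State in Sections 3 and 5.4, in the same words, that every enrolled patient, infused or not, is followed for at least 24 months from that origin.

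The cost is protocol wording and survival contacts for the few enrolled patients who are not infused. If infusion starts g days after enrollment, follow-up under Section 5.4 already covers 24 months from enrollment for infused patients, so their schedule need not lengthen. The estimates may be slightly less favorable, because events before infusion now count. No dosing or clinical rule changes.
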